## Abstract

**Introduction::**

The occurrence of post-stroke emotional problems is significant during the early post-stroke stage and affects the recovery of functionality among the survivors. Because stroke survivors require active engagement in rehabilitation to optimize the process of neuroplasticity in the initial stage of stroke, there is a need to integrate an intervention, preferably therapists-mediated during rehabilitation, which reduce emotional problems thus improve motivation level among the survivors. One such technique is autogenic relaxation training (ART). ART has been found to reduce anxiety and depression among patients with several medical conditions. However, its usage in stroke survivors during rehabilitation has been limited to date. Therefore, this study is intended to evaluate the effectiveness of ART in addition to usual physiotherapy in improving emotional state and functional level of stroke survivors during rehabilitation.

**Methods::**

This is an assessor blinded randomized controlled trial comparing 2 intervention approaches namely ART-added physiotherapy (experimental group) and usual physiotherapy (control group). A total of 70 post-stroke patients will be recruited and allocated into either the ART-added physiotherapy or the usual physiotherapy group. The ART-added physiotherapy group will undergo a 20-minute ART session followed by 40 minutes of usual physiotherapy. While the usual physiotherapy group will receive usual physiotherapy alone for 60 minutes. All participants will be treated once a week and are required to carry out a set of home exercises for 2 times per week during the 12-week intervention. Assessment of emotional status and functional independence will be carried out at pre-intervention and week 13 of the intervention with the use of Hospital anxiety and depression scale, Barthel index, and EuroQol-5 dimensions-5 levels. All data will be analyzed using descriptive and inferential statistics.

**Discussion::**

The expected main study outcome is an enhanced evidence-based physiotherapy program that may be used by physiotherapists in the rehabilitation of stroke patients with emotional disturbances.

**Trial registration::**

Australian New Zealand Clinical Trials Registry, ACTRN12619001664134 (last updated on 28/11/2019).

## Introduction

1

Stroke is one of the disabling conditions among adult and older populations worldwide.^[1]^ Post-stroke rehabilitation, which focus on therapeutic exercises remains the mainstay of treatment aiming to combat post-stroke functional dysfunctions and improve quality of life among stroke survivors.^[2]^ The adherence to the exercises is the key factor of the success in rehabilitation; unfortunately, 65% of stroke survivors fail to adhere to their prescribed exercises due to various reasons including psycho-social problems.^[3–5]^

It is documented that approximately 30% to 45% of stroke survivors have some forms of psycho-social problem such as depression, anxiety, mania, apathy, and fatigue.^[6–8]^ The symptoms may range from relatively minor anxiety to a severe depression. The persistence of these negative consequences often limits the survivors to understand their limitations and post-stroke goals, adopt new skills and adhere to rehabilitation interventions.^[9]^ Post-stroke emotional issues may also influence the working memory performance,^[10]^ mood, and energy levels,^[11]^ and results in negative personality changes such as poor acceptance of disability, poor concentration, being irritable, and unrealistic.^[12,13]^ Eventually, these would affect the post-stroke recovery and quality of life of the survivors.^[14]^

In the past, rehabilitation exclusively focused on motor or movement rehabilitation since it is the most significant problem following a stroke. However, as the mental and psychosocial disability are increasingly recognized as a serious health concern influencing the functionality of the stroke survivors particularly when they return to the community from acute care settings, rehabilitation professionals should now consider these aspects in planning post-stroke activities. Physiotherapists, being the key rehabilitation professional should broaden their roles in post-stroke rehabilitation including recognizing symptoms of mental health and implement suitable strategies to improve emotional state and ensure optimum level of adherence to exercise program.^[3]^

The application of psychological interventions in physiotherapy practice is still at a primitive stage to date.^[2,15]^ Existing physiotherapy practice in stroke rehabilitation shows that emotional factors are not well addressed even though they have been found to negatively impact on daily functioning, quality of life, and functional outcome.^[16,17]^

Relaxation exercises have an important role in reducing the negative effects of the emotional problems arising in many neurology-related conditions such as stroke, cerebral palsy, Parkinson disease, and spinal cord injury.^[18–20]^ There are many available relaxation techniques such as autogenic relaxation training (ART), relaxation–biofeedback, progressive relaxation exercise (PRE), and relaxation—hypnosis. ART is the most commonly used relaxation technique which is found to produce positive effects on various conditions such as anxiety, depression, hypertension, and pain.^[21,22]^ ART is a simple, self- administered exercises with low-cost of implementation which can easily be administered by physiotherapists. To date, very few studies are available on the effects of ART in stroke population.^[23,24]^ The ART when added into a usual physiotherapy could possibly reduce anxiety and provide a positive outlook which may consequently facilitate greater functional independence. The aim of the study is to investigate the effectiveness of the ART when combined with usual physiotherapy in comparison to usual physiotherapy alone. Usual physiotherapy which normally consists of functional training, balance, and gait training is the commonly used therapy for the stroke population.

## Methods

2

### Study design and setting

2.1

A single blind randomized controlled trial will be used as the study design to identify the effectiveness of the ART in addition to usual physiotherapy on post-stroke individuals and comparing this with usual physiotherapy alone. This study will be conducted at Universiti Kebangsaan Malaysia Medical Center, a teaching hospital in the Klang Valley, Malaysia. A one group experimental pilot study will be conducted to identify the feasibility of the ART-added physiotherapy protocol before the main study commences. The flow of the study is shown in Fig. 1.

**Figure 1 F1:**
[figure not shown]
Flow of the study.

### Study participants

2.2

The study participants will be selected with the assistance from physiotherapists in Universiti Kebangsaan Malaysia Medical Centre (UKMMC) using a simple random sampling method from stroke patients’ registry which is maintained by the rehabilitation unit of the hospital.

The inclusion criteria are as follows:

First-time stroke, diagnosed clinically by a medical physician.Sub-acute phase post-stroke (2 weeks–3 months), medically stable condition.Age 40 to 75 years.Montreal cognitive assessment score ≥26.

The exclusion criteria are:

Having receptive aphasia.History of any psychosomatic disorders.Score ≥4 on a modified Rankin scale (wheelchair or bed bound).

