### Participants allocation

2.3

Participants allocation will be conducted by an independent researcher using a stratified randomization method. Sequentially numbered, opaque sealed envelopes will be used to assign the participants into either an experimental group (ART-added physiotherapy) or a control group (usual physiotherapy alone—UP). Stratification variables are age, consisting of adult (40–59 years) and older age (50–75 years), and disability level, namely 1 to 2 (no significant disability or slight disability) and 3 (moderate disability). Therefore, both the ART-added physiotherapy and UP trial arm will consist of subjects with the 2 age and disability levels.

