### Interventions

2.4

The experimental group will receive ART session for 20 minutes, followed by usual physiotherapy for 40 minutes. The ART will be conducted in a quiet room. Participants will be positioned in supine lying or sitting throughout the session and should empty his or her bladder before the session. During the ART session, the participants are asked to loosen any tight clothing, remove watch, spectacles, and stockings. The participants are allowed to close their eyes but not fall asleep while listening to the ART instructions.

Generally, there are 6 standard exercise tasks in ART:

Tranquility exercise: should create a state of silence and concentration. Typical imagination: “I am calm. Nothing can disturb me.”Heaviness exercise: should create a sense of heaviness in the limbs. Typical imagination: “My arms and legs are heavy.”Warmth exercise: sense of heat in the limbs. Typical imagination: “My arms and legs are warm.”Breathing exercise: concentrated breathing. Typical imagination: “My breath is calm and regular.”Heart exercise: Should cause further sedation. Typical imagination: “My heart beats calmly and regularly.”Solar plexus exercise: concentration on the celiac plexus should deepen the relaxation. Typical imagination: “The center is warm.”

After the ART session, the participants will be asked to remain on the training mat for 5 minutes before starting usual physiotherapy interventions. Usual physiotherapy in this study consists of general functional exercises, balance, upper limb, and gait training.

The control group will undergo usual physiotherapy alone for 60 minutes. The content of usual physiotherapy is similar to that given to the ART-added physiotherapy group. Blood pressure of each participant will be recorded before and after the intervention session. The participants are instructed to report any unusual feelings that they may experience such as giddiness, nausea, or shortness of breath to the physiotherapist during the intervention sessions.

Both groups undergo the given intervention for 3 times per week (1 supervised and 2 non-supervised) for 12 weeks, for a total duration of 1 hour per session. Monitoring of the participants will be done weekly during the supervised session to ensure adherence to the non-supervised in-home sessions and to assess the occurrence of any adverse effect.

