### Assessment of outcomes

2.6

Participants will be assessed at baseline and at week 13 of interventions by a therapist who is blinded to the group allocation and trained to conduct the standardized tests. The recorded baseline assessment data will not be accessible to the blinded assessor at post-trial assessment in view to avoid assessment bias.

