### Data analysis

2.8

All data will be entered into IBM Statistical Packages for Social Sciences (SPSS) version 25.0. Intention-to-treat (ITT) method will be used; all the participants recruited at baseline will be included in the outcome analysis. Using ITT, missing data will be replaced with last observation carried forward. Socio-demography and health profile of the participants will be analyzed descriptively and reported as frequencies (percentages) and mean (standard deviation) or median (inter-quartile range). The effects of the interventions will be analyzed using mixed model ANOVA and reported as main time, group, and time–group interaction effects. The level of significance will be set as *P* < .05 for all results.

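### Entry spans 2 weeks to 3 months after stroke, but time since stroke is neither a stratification factor nor a term in the stated model; adding it as a pre-specified covariate would gain precision at almost no cost.

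*Protocol article*

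**What the plan says.** Only the protocol article is at hand. Four of its statements bear on this point.

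- **Entry (2.2 Study participants).** Patients have had a first stroke and must be in this window: "Sub-acute phase post-stroke (2 weeks–3 months), medically stable condition".
- **Allocation (2.3 Participants allocation).** "Stratification variables are age, consisting of adult (40–59 years) and older age (50–75 years), and disability level". No other stratification factor is named.
- **Analysis (2.8 Data analysis).** "The effects of the interventions will be analyzed using mixed model ANOVA and reported as main time, group, and time–group interaction effects". No covariate is named.
- **Timing (2.4 Interventions, 2.6 Assessment of outcomes).** Treatment lasts 12 weeks. "Participants will be assessed at baseline and at week 13 of interventions".

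The Introduction part of the Abstract gives the reason for acting early. It says emotional problems matter in the early period after stroke, and that survivors need "active engagement in rehabilitation to optimize the process of neuroplasticity in the initial stage of stroke".

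**The concern.** If 3 months is taken as 13 weeks, the entry window is about 11 weeks wide. The week-13 assessment then falls about 15 weeks after stroke for the earliest entrant (2 + 13) and about 26 weeks for the latest (13 + 13). On the trial's own rationale, the stage after stroke affects mood and the capacity to recover. Expected change in HADS, MBI and EQ-5D-5L over the same 13 weeks may therefore differ between early and late entrants in both arms, whatever the effect of ART.

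Every patient's time since stroke has to be established to confirm eligibility, but neither the allocation nor the stated model uses it. Two things follow. Any outcome variation that time since stroke could explain remains in the error term. And if the arms differ in it by chance, the estimate is not corrected for that difference. With 70 patients and no stated allowance for dropout, precision is worth having when it is free.

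**Working it through.** **Inputs.** From the article: N = 70, effect size 0.34, significance level 0.05, power 80% (2.7); entry from 2 weeks to 3 months (2.2); two assessments (2.6). Assumed, because the article does not say: 3 months = 13 weeks, 1:1 allocation (35 per arm), the distribution of entry times, and R², the share of residual outcome variance that time since stroke explains.

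**Step 1. Reproduce the planned sample size.** The article does not say which metric the 0.34 is in, and two readings give 70.

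- Read as Cohen's f (d = 2 × 0.34 = 0.68), one between-group comparison: noncentrality λ = f²N = 0.1156 × 70 = 8.09 on 1 and 68 df. Power is 80.1%, so N = 70.
- Read as d (f = 0.17), time-by-group interaction, two measurements, correlation 0.5 assumed: λ = 0.17² × 2/(1 − 0.5) × 70 = 0.1156 × 70 = 8.09. Again N = 70.

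Because λ is the same, the power figures in Step 3 serve either reading. In the second, R² is a share of change-score variance.

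**Step 2. Chance imbalance between arms.** For uniform entry over weeks 2 to 13:

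- SD = 11/√12 = 3.18 weeks.
- SE of the arm difference = 3.18 × √(2/35) = 0.76 weeks.
- 95% range = ±1.96 × 0.76 = ±1.5 weeks.
- Chance of a gap over 1 week in either direction = 19%.

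If entry bunches at one end of the window, the SD is smaller. With SDs of 2.1 to 2.6 weeks, the same formula gives SEs of about 0.5 to 0.6 weeks and 95% ranges of about ±1.0 to ±1.2 weeks.

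**Step 3. What it does to the comparison.** The chance shift in the arm difference, in outcome SDs, has a 95% range of ±1.96 × √R² × √(2/35). It depends on R² and not on the shape of the entry distribution. After adjustment λ becomes 8.09/(1 − R²) on 1 and 67 df, and the standard error is multiplied by √(1 − R²).

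| Assumed R² | Chance shift (95% range, SD) | SE multiplier | λ | Power at N = 70 | N for 80% power |
|---|---|---|---|---|---|
| 0 (unadjusted) | – | 1 | 8.09 | 80% | 70 |
| 0.05 | ±0.10 | 0.97 | 8.52 | 82% | 68 |
| 0.10 | ±0.15 | 0.95 | 8.99 | 84% | 64 |
| 0.20 | ±0.21 | 0.89 | 10.1 | 88% | 58 |

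**Step 4. Is the unadjusted test still valid?** Simulation with no treatment effect (5,000 runs each, 35 per arm) gave rejection rates of 4.9% at R² = 0.2 and 5.3% at R² = 0.4 without adjustment, and 4.7% and 4.6% with it. All are close to the nominal 5%. The chance shifts in Step 3 are already part of the unadjusted standard error.

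**The case against.** The strongest reply is that nothing here is an error. Randomisation balances time since stroke on average, and the P value already allows for chance imbalance. That stands. A reader might infer that uneven natural recovery biases the comparison or inflates false positives; the design and the simulation do not support that.

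A second reply is that the size is assumed. That also stands: the article gives no correlation between time since stroke and any outcome. At R² = 0.05 the gain is only two percentage points of power. Stratifying by disability may already capture part of the effect, though patients at 2 and at 13 weeks with the same disability level share a stratum.

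A third reply is that covariates are often left to an analysis plan, and 2.8 does not exclude them. This has some force. But the article does state its stratification factors and the effects its model will report, so the proposal changes something stated. If an unseen plan already names this covariate, the point is met.

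A reader might also infer that much of the treatment falls outside the early stage the trial is meant to address. The article does not support this. It never says when the early or initial stage ends. The 3-month limit governs entry, and no section requires treatment to finish within it. The aims and expected conclusions concern stroke survivors generally and are not confined to that stage.

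**Conclusion.** The point holds as a missed gain in precision, not as a threat to validity. A baseline variable that the trial's own rationale marks as relevant, and that eligibility already requires, is absent from both the allocation and the stated analysis. Under uniform entry and 35 per arm, the arms could differ by up to about 1.5 weeks in mean time since stroke (95% range), and the stated model would leave that uncorrected.

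The benefit of adjusting is small at R² of 0.05 to 0.10 (power 82–84%) and material at about 0.20 (88%). Which applies cannot be settled from the article, and it may differ between HADS, MBI and EQ-5D-5L. The recommendation rests on the low cost of the change rather than on any one value of R².

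**What to change.** In 2.8, pre-specify weeks from stroke to randomisation as a continuous baseline covariate in the between-arm analysis of HADS, MBI and EQ-5D-5L, in one of two forms:

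- an ANCOVA of the week-13 score on baseline score, group and time since stroke; or
- the mixed model as stated, plus time since stroke and its interaction with assessment time.

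In the second form the interaction term is essential. A covariate that is constant within a patient, entered as a main effect only, adjusts the group effect averaged over both assessments and leaves the time-by-group effect unadjusted.

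The choice should be fixed before outcome data are seen, because adding the covariate after noticing an imbalance would be data-driven. The covariate costs one degree of freedom in the between-arm test of change (68 to 67 in the mixed model) and a sentence or two of text. It needs no new data, patients or visits, and eligibility, allocation and treatment stay as they are. I would not add a group-by-time-since-stroke interaction, which would be very imprecise with 70 patients.

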### Participants allocation

2.3

Participants allocation will be conducted by an independent researcher using a stratified randomization method. Sequentially numbered, opaque sealed envelopes will be used to assign the participants into either an experimental group (ART-added physiotherapy) or a control group (usual physiotherapy alone—UP). Stratification variables are age, consisting of adult (40–59 years) and older age (50–75 years), and disability level, namely 1 to 2 (no significant disability or slight disability) and 3 (moderate disability). Therefore, both the ART-added physiotherapy and UP trial arm will consist of subjects with the 2 age and disability levels.

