### Sample size

2.7

The one group experimental pilot study involves 20 participants which is considered adequate to assess the feasibility of a pilot intervention.^[30]^ For the main study, 70 eligible stroke participants will be recruited. The sample size of 70 was estimated using GPower software and based on mixed-model analysis of variance (ANOVA) test with effect size of 0.34 (Manzoni 2008),^[31]^ significance level *P* < .05 and study power 80%.

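### The two age strata for randomisation overlap at 50–59 years, so the stratum, and with it the envelope series, is undefined for patients of that age

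*Protocol article*

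**What the plan says.** Section 2.2 (Study participants) sets the age criterion as "Age 40 to 75 years". Its only disability limit is an exclusion: "Score ≥4 on a modified Rankin scale (wheelchair or bed bound".

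Section 2.3 (Participants allocation) has an independent researcher allocate patients "using a stratified randomization method", with opaque, sealed envelopes numbered in sequence. The age bands are given as "Stratification variables are age, consisting of adult (40–59 years) and older age (50–75 years". The second factor is "disability level, namely 1 to 2 (no significant disability or slight disability) and 3 (moderate disability". The section concludes that each "trial arm will consist of subjects with the 2 age and disability levels", so the design has two age levels crossed with two disability levels, four cells in all.

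Section 2.7 (Sample size) gives the total: "For the main study, 70 eligible stroke participants will be recruited". Section 2.8 (Data analysis) plans a mixed-model ANOVA with time, group and interaction effects and names no stratum term.

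**The concern.** Strata must be mutually exclusive and must cover everyone eligible; otherwise the allocation rule does not yield one answer per patient. Stratified allocation from sequential envelopes implies one series per cell, although the article does not spell this out. For a patient aged 50 to 59, two series are valid under the printed bands and no rule picks one.

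Two things are at stake. First, whoever opens the envelope makes a choice that a pre-specified sequence is meant to remove. Second, if patients of the same age go sometimes to one list and sometimes to the other, the lists no longer separate younger from older patients cleanly, and the control of age balance loosens.

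This is not a detail that an article leaves to a fuller document. The article does give the bands, and as given they are inconsistent.

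**Working it through.** **Inputs.** Eligible ages 40 to 75 (section 2.2); age bands 40–59 and 50–75, and disability levels 1–2 and 3 (section 2.3); total of 70 (section 2.7).

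**The plan's own figure.** The total of 70 serves here only as a denominator. Section 2.7 bases it on a "mixed-model analysis of variance (ANOVA) test with effect size of 0.34", 5% significance and 80% power. Reading 0.34 as Cohen's f, a two-group F test on a single measurement has noncentrality 70 × 0.34² = 8.09 on 1 and 68 degrees of freedom. Its power is 0.801, and 70 is the smallest even total that reaches 80%. The figure is reproduced in that form and has no bearing on the strata.

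**Age overlap.**
- Eligible whole-year ages: 75 − 40 + 1 = 36.
- Ages in the first band: 59 − 40 + 1 = 20. Ages in the second: 75 − 50 + 1 = 26.
- Ages in both: 20 + 26 − 36 = 10, namely 50 to 59.
- Ages in exactly one band: 36 − 10 = 26.

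**Share of patients.** The article gives no age distribution, so any number of patients is an assumption.

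| Assumed share aged 50–59 | Patients out of 70 |
|---|---|
| 10% | 7 |
| 10/36 = 27.8% (even spread over ages) | 19.4 |
| 40% | 28 |

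**Candidate corrections.** Changing one digit removes the overlap in either of two ways:
- 40–59 and 60–75: 20 + 16 = 36 ages, each in one band.
- 40–49 and 50–75: 10 + 26 = 36 ages, each in one band.

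Both cover the eligible range, and they put patients aged 50 to 59 in opposite strata. The text does not show which was meant. The flow figure is not available here and could not be checked.

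**Disability levels (minor).** Section 2.3 does not name the scale. Its levels stop at 3, just below the modified Rankin exclusion in section 2.2, so that scale is the natural reading. If it is meant, and if it has a level 0 (which the article does not state), then level 0 is eligible but has no stratum. On that reading, 36 ages × 4 scores = 144 combinations:
- exactly one stratum: 26 × 3 = 78
- two strata: 10 × 3 = 30
- no stratum: 36 × 1 = 36

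These are counts of combinations, not of expected patients.

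**The case against.** The best defence is that this is a one-digit slip. Section 2.3 plainly intends two distinct age levels, ages 40–49 and 60–75 are unaffected, and the researcher may be working from a correct list. That is likely, and it means that the scheme is faulty in one band rather than unusable as a whole. But two different one-digit corrections are available, so a reader cannot recover the rule.

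The defence is stronger on consequences. Three larger claims might be inferred, and the document supports none of them.

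- **That concealment is broken.** Choosing between two sealed series does not reveal the next assignment in either. The choice could be exploited only if the next assignment were predictable, for example from small known blocks, and the article gives no block size. An independent researcher makes the allocation. Discretion exists; subversion is not shown.
- **That balance on age is defeated.** Each series still assigns at random, patients aged 40–49 can enter only the younger list, and patients aged 60–75 only the older. Balance is weakened, not lost, and no direction of bias follows.
- **That the planned analysis is damaged.** Section 2.8 names no stratum-adjusted analysis, so an undefined stratum variable harms nothing that the article specifies.

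The disability point also deserves its modest place. It depends on an unnamed scale and on a level that the article never mentions, and few patients from a rehabilitation registry are likely to be at that level.

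**Conclusion.** The age strata are wrong as written. Ages 50 to 59, which are 10 of the 36 eligible whole-year ages, belong to two strata, and the envelope series for those patients is undefined. The overlap is read directly from the text and needs no assumption. How many of the 70 patients it touches is unknown; about 19 follows only from an even spread of ages.

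The consequence is discretion over the choice of series and weaker control of age balance, with random assignment inside each series intact. It still needs correcting, because the error sits in the operative allocation rule and is harder to repair once patients have been allocated.

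The disability levels are a side note, conditional on the modified Rankin scale being meant.

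**What to change.** Before envelopes are prepared:

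1. State two age bands that do not overlap and together cover 40 to 75 years. The sponsor must say whether the boundary is 49/50 or 59/60; both fit the eligible range, and this review cannot choose between them.
2. Check the envelope series against the four corrected cells. If allocation has already begun, record which list was used for each patient aged 50 to 59.
3. Include the corrected stratification factors in the analysis model. This accompanies the correction; it does not repair a stated analysis. Two binary factors use 2 of the 68 residual degrees of freedom for the group comparison (70 − 2).
4. Name the disability scale in section 2.3 and reconcile its levels with the eligibility criteria in section 2.2, so that every eligible score has a stratum.

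The cost is a sentence or two of text and one check of the envelopes. The sample size does not change.
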